#### Secondary outcomes

2.8.2

##### Obesity-Related indicators

2.8.2.1

Weight; BMI (weight/(height); body fat percentage; basic metabolism value; WC; hip circumference(HC); waist-to-hip ratio (WC/HC); Visceral fat area; body fat; and obesity degree will be measured on week 0, 1, 2, 3, and 4.

#### The IWQOL-Lite scale

2.8.3

The IWQOL-Lite scale will be measured on week 0, 1, 2, 3, and 4. The lower the total score, the lighter the clinical symptoms of the patient.

#### The syndrome score of TCM

2.8.4

The syndrome score of TCM will be adopted as the criterion of syndrome determination according to the diagnostic and therapeutic evaluation standard of simple obesity revised by the 5th National Obesity Research Conference in 1997. The total score will be then calculated and the unit will be expressed in points. The main clinical symptoms of simple obesity of spleen deficiency and dampness resistance type were divided into 4 levels, which include no (0 point), mild (1 point), medium (2 points) and heavy (3 points). Measurements will be made on week 0, 1, 2, 3, 4.

### Safety assessments

2.9

When any trial-related adverse events including skin rash, skin allergy, and infection occur during this clinical trial, they will be recorded by the clinicians, and the researchers should make sure that the participant is properly and timely medically treated. Three experts from different fields from Hubei Provincial Hospital of TCM compose an independent Safety Monitoring Board, who has the right to make the final decision to terminate the study. All these experts will monitor the safety and performance of this trial to make sure that the study goes smoothly.

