## Abstract

**Introduction::**

Obesity is a global public health issue, which results in many health complications. Moxibustion may serve as an alternative management for simple obesity, where pharmacological therapy is always difficult to be accepted by the majority of obese patients based on its safety. However, the effects of herb-partitioned moxibustion as obesity intervention have not been confirmed. This study is designed as a single-blinded, 3-dummy randomized controlled trial to evaluate the efficacy and safety of herb-partitioned moxibustion plus lifestyle modification treatment in patients with simple obesity.

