**Methods and analysis::**

This study will be a randomized, controlled trial conducted from April, 2019 to April, 2021 that includes 108 participants who have simple obesity and meet the eligibility criteria. The participants will be randomly divided into 3 treatment groups: heat application group, medicated plaster group, or herb-partitioned moxibustion group. Each treatment will last 4 weeks. The primary outcomes will be the clinical effectiveness. The secondary outcome measures include participants’ obesity-related indicators, the IWQOL-Lite scale, and the syndrome score of Traditional Chinese Medicine. Adverse events will be recorded during the intervention period.

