### Study procedure

2.3

This study consists of 2 phases including:

(1)a 4-week screening phase (week 0);(2)a 4-week treatment phase (week 1–4).

When potential participants show interest in this study, they will be instructed to record their medical history in a screening form. Thereafter, they will be invited to complete an eligibility assessment by trial investigators; next, eligible participants will be enrolled and written informed consent will be provided to them. Participants who meet the inclusion criteria and exclusion criteria will be enrolled, grouped, and given a 4-week interventions. The schedule of enrolments, allocation and assessments is given in Table 1 below.

**Table 1 T1:** The schedule of enrolments, allocation, and assessments.

Phase	Enrolment/allocation	The treatment period			
Timepoint	Wk 0	Wk 1	Wk 2	Wk 3	Wk 4
Informed consent	X				
Eligibility screening	X				
Demographic data	X				
Obesity-related indicators	X	X	X	X	X
The IWQOL-Lite scale	X	X	X	X	X
The syndrome score of TCM	X	X	X	X	X
Record of treatment		X	X	X	X
Drug combination∗	X				
Adverse event	X				
Compliance evaluation	X				
Research completion	X				
Investigator review	X				
Supervisor review	X				

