### Blinding and informed consent

2.6

In this study, the participants will be informed that they will have a 1/3 chance of being allocated to receive 1 of the 3 treatments: heat application, medicated plaster, and herb-partitioned moxibustion. The data statisticians and research staff involved in data collection and data analysis will be blinded to the assignment of participants’ group throughout the entire study. However, the participants and therapists cannot be masked due to the nature of these interventions, but they will be trained not to share any information with other participants, researchers, and the data statistician regarding treatment procedures and responses.

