In the past 50 years, it has been illustrated that obesity is mainly caused by a dysfunctional relationship between Spleen, Liver, Kidney, and the sanjiao (triple energizer), and its pathogenesis is closely related to the blood vessel obstruction by Qi deficiency and phlegm dampness stagnation, which might be caused by various internal and external factors such as stasis of liver Qi, deficiency of spleen, or over intake of greasy flavour. Based on the foundation of this theory, the therapeutic principle of simple obesity is invigorating spleen to remove dampness and relieving Qi stagnancy in Liver to remove blood stasis.^[21,22]^ We designed this clinical trial to evaluate the efficacy and safety of partitioned moxibustion plus lifestyle modification treatment for patients with simple obesity. The participants’ obesity-related indicators, the IWQOL-Lite scale, and the syndrome score of TCM. Adverse events will be recorded and reported.

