Moxibustion also has been widely used in China for more than 2500 years. Herb-partitioned moxibustion is a critical component of moxibustion therapy in TCM. It treats diseases by placing a piece of herb formula on the patient's acupuncture points and then igniting a moxibustion tube on the herb formula. While to be different with the traditional partitioned moxibustion, herb-partitioned moxibustion used in this study can not only produce heat stimulation and infrared radiation necessary for moxibustion, but also effectively avoid smoke pollution and open fire danger, and can also play the role of medicine. Therefore, we considered whether this new type of herb-partitioned moxibustion therapy could be more effective in improving related symptoms in patients with simple obesity. There is a lack of relevant clinical evidence in this regard, which we aim to address in this clinical trial. Thus, we will provide supporting evidence for this new type of herb-partitioned moxibustion therapy to treat simple obesity. However, this protocol still has some limitations. Firstly, because of the limited funding and the lack of adequate preliminary studies, this survey has been designed as a single-center pilot study with a small sample size. Secondly, although all outcomes will be measured and recorded by an independent researcher in order to minimize the risk of detection bias, the double-blind procedure cannot be completely adopted for the acupuncture therapist. Nevertheless, we expect that this randomized controlled trial will be able to provide some new evidence regarding this modern new herb-partitioned moxibustion therapy in the treatment of simple obesity.

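### Section 2.9 provides for recording only trial-related adverse events, while the abstract and discussion set no such limit, so events judged unrelated may go unrecorded

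*Protocol article*

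**What the plan says.** The abstract's introduction gives the trial's purpose as "to evaluate the efficacy and safety of herb-partitioned moxibustion plus lifestyle modification treatment in patients with simple obesity", so safety is a stated objective.

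Three places in the protocol article say in words which adverse events are recorded:

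- Section 2.9 (Safety assessments): "When any trial-related adverse events including skin rash, skin allergy, and infection occur during this clinical trial, they will be recorded by the clinicians".
- Abstract, Methods and analysis: "Adverse events will be recorded during the intervention period".
- Discussion: "Adverse events will be recorded and reported".

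Table 1 (section 2.3) also has a row labelled "Adverse event", with no qualifier.

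On masking, section 2.6 says that "the participants and therapists cannot be masked due to the nature of these interventions". It also says: "The data statisticians and research staff involved in data collection and data analysis will be blinded to the assignment". The limitations paragraph of the discussion adds that "all outcomes will be measured and recorded by an independent researcher in order to minimize the risk of detection bias".

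**The concern.** Section 2.9 is the only passage that works as an instruction for safety recording: it says what is recorded and by whom. The abstract and discussion are summary statements. Staff who follow section 2.9 as written would first decide whether an event is related to the trial, and the rule then covers it only if the answer is yes. The article does not say who decides or on what basis.

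That order matters here for two reasons. First, the three arms give heat alone, herbs alone, or both, and participants and therapists know which. How readily an event is put down to the trial may therefore depend on the arm. Second, an event filtered out before recording leaves no trace, and no later analysis can restore it. Section 2.4.4, for instance, foresees serious illness found during treatment and handles it as a reason for dropout. Section 2.9 brings such an illness into the safety record only if it is thought to be trial-related.

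**Working it through.** The plan gives no adverse event rate and no safety test, so there is no figure of its own to reproduce. The check is a comparison of texts, followed by an illustration on assumed figures.

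**Comparison of the statements**

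| Place | Events covered | Period | Recorder |
|---|---|---|---|
| Section 2.9 | trial-related only | the clinical trial | the clinicians |
| Abstract | no limit | the intervention period | not stated |
| Discussion, on adverse events | no limit | not stated | not stated |
| Table 1 row | no limit | layout not reliable as extracted | not stated |

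1. The scope differs: section 2.9 has a qualifier that the other three places lack.
2. No passage makes explicit provision for an event judged unrelated. The unrestricted statements would include it; section 2.9 does not.
3. No passage says who assesses relatedness or by what criterion.
4. Participants and therapists are unmasked, and staff involved in data collection are masked. The masking status of the clinicians in section 2.9 is not stated.

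**What unequal attribution would do**

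Let p be the true risk of an event in an arm, and a the probability that such an event is judged trial-related and so recorded. Then

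recorded risk = p × a

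recorded risk ratio (arm A to arm B) = (pA × aA) / (pB × aB) = true risk ratio × (aA / aB).

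All values of p and a below are assumptions. The arm size of 36 is from section 2.1.

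- Equal attribution, p = 20% and a = 65% in both arms: 0.20 × 0.65 = 13% in each. Events are under-counted, but the risk ratio stays at 1.
- Unequal attribution, p = 20% in both arms, a = 50% and 80%: 0.20 × 0.50 = 10% and 0.20 × 0.80 = 16%. This is a spurious difference of 6 percentage points and a recorded risk ratio of 0.50 / 0.80 = 0.625, where the truth is 1. In expected counts it is 36 × 0.10 = 3.6 against 36 × 0.16 = 5.8, where both should be 36 × 0.20 = 7.2.
- The same rates the other way round: 0.80 / 0.50 = 1.6. The direction is open.

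**What under-recording would do within one arm**

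With an assumed true risk of 5%, the chance that the event occurs at least once among 36 participants is 1 − 0.95^36 = 0.842. If only half of such events are attributed to the trial, the recorded risk is 2.5% and the chance of at least one recorded event is 1 − 0.975^36 = 0.598. These two figures concern detection in a single arm and say nothing about bias between arms.

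**The case against.** The best defence is that section 2.9 says trial-related events will be recorded but does not say that others will not be. The abstract and discussion are unrestricted, so the qualifier may be loose wording. The text is also a journal article, and causality grading and case report form fields are commonly left to the full protocol. This stands in part: loss of events is possible, not certain, and the missing grading detail is not itself a fault. It does not remove the point, because the qualifier is a stated rule that conflicts with other statements in the same article.

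A reader might infer more than the documents support:

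- *That unmasked clinicians make the judgement.* Section 2.6 names participants and therapists as unmasked and says data-collection staff are masked. Nothing says that the clinicians of section 2.9 are the therapists, or that they judge relatedness. The discussion assigns the recording of all outcomes to an independent researcher, without saying whether adverse events count as outcomes.
- *That Table 1 restricts adverse event recording to week 0.* The row for research completion carries the same single mark and cannot belong to week 0, so the layout was very probably broken in extraction.
- *That thermal injury is left out.* The list in section 2.9 is introduced as examples, and a burn from a heated sticker would be trial-related on any reading.

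**Conclusion.** The concern holds as an inconsistency with a practical consequence. Section 2.9 limits recording to trial-related events, the abstract and discussion do not, and the literal reading of section 2.9 places an undefined causality judgement before recording in a trial whose participants and therapists know the treatment. Events judged unrelated may be missed, and the extent may differ by arm.

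Neither the size nor the direction of any bias can be derived from the documents. With equal attribution in the arms, events are under-counted and the risk ratio is undistorted. With unequal attribution, it is distorted by the ratio of the attribution rates. The 5%, 20%, 50%, 65% and 80% used above are assumptions chosen for illustration. The conclusion does not rest on them; it rests on the wording of section 2.9 and on staff following it as written.

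**What to change.** Reconcile the passages by deleting the trial-related qualifier in section 2.9, so that all adverse events in every arm are recorded whatever their suspected cause. Assess relatedness afterwards and keep it as a separate field. Report all events and related events by arm.

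Keep the period that section 2.9 already gives, the whole trial. A cut-off at week 4 could narrow it, since section 2.7.1 gives the lifestyle component 8 weeks and sections 2.7.2 to 2.7.4 allow applications to be delayed.

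The cost is one changed sentence in section 2.9, a short statement on relatedness and reporting, and a few more case report form entries. No visits are added, because section 2.1 already has participants treated on three days a week.

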### Data management

2.10

All researchers including the physicians, data collectors, data entry personnel, outcome assessors, and data statisticians will receive special training about the data management and standard procedure. During the recruitment period, the baseline characteristics of participants will be recorded in case report forms (CRF)s by our data collectors and the data manager will check all these data. When the treatment period completes, the data of all participants will have been recorded on the original CRFs and then 2 data entry personnel will enter these data into Excel spreadsheets independently, following which the data manager will cross-check these data sets to ensure accuracy. A corresponding computer database will be established and the medical records of this clinical trial will be input and stored by researches in a password-protected electronic database, and be kept strictly confidential. A member in the study team who is not involved in these data collection will check the database data and source documents. The hard copies of all the clinical data and CRFs will be stored in a fixed locker.

### Sample size calculation

2.11

In a previous study, the effective rate of simple obesity in the herb-partitioned moxibustion group was *P*1 = .80. The effective rate of the heat application group was *P*2 = .65, and the effective rate of the medicated plaster group was *P*3 = .6. PASS V.11 software (NCSS, Kaysville, UT) was used to calculate that, based on 80% power to detect a significant difference(α = 0.025, 1 sided), 33 participants will be required for each group. Allowing for a 10% withdrawal rate, we plan to include a total of 108 participants with 36 participants in each group.

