### Statistical analysis

2.12

The data of all participants will be conducted in the final statistical analysis which will be in accordance with the per-protocol principle and the intent-to-treat principle. The data statisticians will be blinded to the group allocation. The SPSS software v19.0 (Statistics 19.0, SPSS, IBM Corp., Chicago, IL) will be used for statistical processing. Measurement data will be presented in the form of mean ± standard deviation, while count data will be expressed as percentage and number. The continuous variables, such as participants’ obesity-related indicators including weight, BMI (weight/height), body fat percentage, basic metabolism value, WC, HC, waist-to-hip ratio (WC/HC), visceral fat area, body fat, and obesity degree will be presented as mean ± SD. Between-group comparisons will be performed by ANOVA or its non-parametric equivalents on changes from baseline to after treatment. Intra-group comparison will be performed by using the Kruskal–Wallis test. All statistical tests will be performed on both sides, and the difference will be considered statistically significant when *P* < .05.

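### 33 per group does not give 80% power for the plan's own effective rates; power is about 27% against heat and 42% against plaster

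*Protocol article*

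**What the plan says.** Section 2.11 (Sample size calculation) takes three rates from a previous study. For the combined treatment it reports that "the effective rate of simple obesity in the herb-partitioned moxibustion group was *P*1 = .80". Both comparators are set lower, heat at 0.65 and plaster at 0.60. The target is "based on 80% power to detect a significant difference(α = 0.025, 1 sided", and the stated result is that "33 participants will be required for each group". The final step, which turns this into the enrolled number, reads: "Allowing for a 10% withdrawal rate, we plan to include a total of 108 participants with 36 participants in each group". The section does not say which comparison the 80% refers to or which PASS procedure was run.

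Section 2.12 (Statistical analysis) adds: "All statistical tests will be performed on both sides, and the difference will be considered statistically significant when *P* < .05". For a pairwise comparison, two-sided 0.05 is the same threshold as one-sided 0.025, so the two sections agree on the error rate that matters here.

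The Introduction states a superiority hypothesis: the combination should do better than its components alone. No non-inferiority margin appears anywhere. The Discussion says that "this survey has been designed as a single-center pilot study with a small sample size".

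**The concern.** Differences of 15 and 20 percentage points between proportions of 0.60 to 0.80 normally need a sample well above 33 per group, so the figure looked too small by a wide factor. Every input is printed in section 2.11, so the calculation can be repeated without the analysis plan or the PASS output.

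What is at stake is how the result will be read. A non-significant comparison in a trial said to have 80% power is taken as fair evidence against the assumed effect; at 27% or 42% power it says little. In the other direction, a comparison in so small a trial reaches significance only when the observed difference exceeds the planned one, so a positive result will tend to overstate the effect. The Discussion's description of a small pilot also sits badly beside a claim of 80% power.

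**Working it through.** **Inputs (section 2.11).** p1 = 0.80; p2 = 0.65 (heat) or 0.60 (plaster); one-sided alpha 0.025, z = 1.960; power 80%, z = 0.8416; equal allocation (section 2.1).

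**Sample size formula.** With p̄ the mean of the two rates and d their difference,

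n = [1.960·√(2p̄(1−p̄)) + 0.8416·√(p1(1−p1) + p2(1−p2))]² / d²

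- Against heat: p̄ = 0.725, d = 0.15. √0.39875 = 0.6315 and √0.3875 = 0.6225. n = (1.2377 + 0.5239)² / 0.0225 = 137.9, so **138 per group**.
- Against plaster: p̄ = 0.70, d = 0.20. √0.42 = 0.6481 and √0.40 = 0.6325. n = (1.2702 + 0.5323)² / 0.04 = 81.2, so **82 per group**.

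The plan's 33 is not reproduced.

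**Power at the plan's size.** Power = Φ{[d√n − 1.960·√(2p̄(1−p̄))] / √(p1(1−p1) + p2(1−p2))}.

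- Heat, n = 33: (0.8617 − 1.2377)/0.6225 = −0.604, power 27.3%. With n = 36: (0.9000 − 1.2377)/0.6225 = −0.542, power 29.4%.
- Plaster, n = 33: (1.1489 − 1.2702)/0.6325 = −0.192, power 42.4%. With n = 36: (1.2000 − 1.2702)/0.6325 = −0.111, power 45.6%.
- Both comparisons significant (400,000 simulated trials, z-tests): about 20% at n = 33 and 21% at n = 36. At least one significant: about 53% and 56%.

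**Other ways to reach 33.**

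| Variant | n per group, vs heat | n per group, vs plaster |
|---|---|---|
| Pooled, one-sided 0.025 | 138 | 82 |
| With continuity correction | 151 | 91 |
| Unpooled variance | 136 | 79 |
| Arcsine | 137 | 81 |
| Bonferroni for two comparisons | 168 | 99 |
| Pooled, one-sided 0.05 | 109 | 64 |
| Unpooled, one-sided 0.05 | 107 | 62 |

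The smallest entry, 62, is nearly twice 33 and uses a looser alpha than the plan's. Exact calculation at n = 33 gives power of 28% and 44% for the z-test, and 19% and 32% for Fisher's test.

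A three-group chi-square test (2 df, alpha 0.05): the mean rate is 0.6833 and the squared deviations sum to 0.02167. The noncentrality at n = 33 is 33 × 0.02167 / (0.6833 × 0.3167) = 3.30, giving 35% power (38% at n = 36). It needs 97 per group. Comparing moxibustion with the two controls combined (rate 0.625) needs 80 in the moxibustion arm.

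**What 33 per group can detect.** Against p1 = 0.80, a comparator rate of 0.48 falls just short of 80% power and 0.47 reaches it: a difference of about 33 points.

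**Smallest significant difference.** At n = 33 and the planning rates, the observed difference must reach about 1.2377/√33 = 21.5 points against heat and 1.2702/√33 = 22.1 points against plaster. Both exceed the assumed 15 and 20.

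**Withdrawal step.** 33/0.9 = 36.7, which rounds up to 37; 36 × 0.9 = 32.4, just under 33. This is a difference of one participant per group and is trivial beside the main error.

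**The case against.** The arithmetic itself is not open to dispute, but several points around it deserve weight.

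- **The figure may come from a procedure the article does not name.** Values near 33 do arise elsewhere: a non-inferiority test against heat with a 15-point margin gives 34, one against plaster with a 10-point margin gives 35, and a one-sample test of 0.80 against 0.60 at one-sided 0.05 gives 33. None fits the text, which states a superiority hypothesis, three parallel arms and no margin. The origin of the 33 remains unknown; what is certain is that the printed inputs do not yield it.
- **The primary outcome has four ordered grades (section 2.8.1).** An ordinal analysis could have different power. It cannot be computed because no grade distribution is given, and section 2.11 plans on binary effective rates. The 27% and 42% are therefore powers for a binary pairwise test. That qualification stands but does not support 33.
- **The plan does not say that both comparisons must succeed.** This also stands: the 20% applies only under that rule, which the Introduction's hypothesis suggests but does not fix. At least one comparison would be significant in slightly more than half of trials, so the statement that significance will probably be missed applies to each comparison taken singly.
- **The Discussion already admits a small sample.** It does, as a limitation, but it does not withdraw the 80% claim.
- **The withdrawal step is a matter of convention.** 33 × 1.10 = 36.3, which some would round to 36. Nothing rests on it.

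**Conclusion.** The sample size statement is wrong as written. On the plan's own rates and alpha, 33 per group gives about 27% power against heat and 42% against plaster, not 80%. The required size is 138 or 82 evaluable per group, roughly 4.2 and 2.5 times the stated number. No superiority calculation tried with these rates comes nearer than 62.

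The conclusion takes the planning rates as given and assumes a binary effective/invalid outcome compared between two arms, or across three by chi-square. The choice of test moves the pairwise power at n = 33 only between 19% and 28% against heat and between 32% and 44% against plaster. This must be corrected, because the stated power governs how a null result will be interpreted.

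**What to change.** Either of two corrections to section 2.11 would resolve this.

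1. **Keep 108 participants and correct the claim.** Replace the 80% statement with the actual power: 27–29% against heat and 42–46% against plaster for 33 to 36 per group, and about 20% if both must succeed. State the detectable difference (about 33 points at 33 per group). Describe the trial as the pilot that the Discussion says it is. A useful option is to report the two risk differences with 95% confidence intervals as the main result. At the planning rates the half-width is 1.96·√(0.3875/36) = 20 points at best and 1.96·√(0.40/33) = 22 points at worst.
2. **Keep the 80% claim and raise the size.** Name the comparison to be powered. Against plaster alone, 82 evaluable or 82/0.9 = 92 enrolled per group; to give each comparison 80% power, 138 evaluable or 138/0.9 = 154 enrolled per group, 462 in total.

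If another PASS procedure or further inputs produced 33, state them. Optionally, note that 36 enrolled leaves about 32 evaluable, or use 37.

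The first route costs only rewording of section 2.11 and of the conclusions that rest on it, and a less favourable stated power. The second costs a much larger trial, which the funding limits given in the Discussion make unlikely.
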